### Ethics and dissemination

2.6

#### Ethical considerations

2.6.1

The study was registered at ClinicalTrials.gov (identifier: NCT07551934; RRID: SCR_002309). The study protocol was approved by the Bioethics Committee at Taras Shevchenko National University of Kyiv (No. 3/03-04-2026). All participants will provide informed consent before any study procedures. Participation will be voluntary, and refusal to participate, withdrawal from the study, or refusal to provide contact information for follow-up will not affect access to medical care, social support, or any other services in accordance with the Declaration of Helsinki (148). Where clinical information is collected from routine clinical records, this will be done only with the participant’s specific consent.

The study involves sensitive information related to reproductive experiences, perinatal mental health, war-related exposure, suicidality-related symptoms, adverse life experiences, and psychosocial circumstances. To reduce participant burden and potential distress, data collection will use standardized web-based questionnaires with programmed routing logic. Participants will be presented only with questions relevant to their reproductive status and study pathway. Participants may discontinue participation at any time. Information on relevant psychological support services, crisis resources, and contact details for the research team will be provided.

An automated safety-response pathway will be embedded in the web-based questionnaire. The pathway will be activated by predefined thresholds for possible acute risk or clinically elevated distress, including an SCI-2-SF score of ≥ 2, EPDS ≥ 13, GAD-7 ≥ 7, IES-R ≥ 30, or City BiTS ≥ 29. When activated, the questionnaire will immediately display a neutral safety message, information on crisis and psychosocial support services, instructions to contact emergency services or the nearest healthcare facility if immediate danger is present, and options to stop, pause, or continue the questionnaire. After receiving the safety message, participants will retain control over their participation. They may stop the questionnaire, pause and return later, skip any item, or continue if they consider it safe and acceptable. The message will also remind participants that participation is voluntary, and that non-completion or withdrawal will have no consequences for their medical care or access to services. All participants, regardless of whether the safety pathway is activated, will receive mental-health and crisis-support information at the end of the questionnaire.

The automated response will not generate notifications to partners, accompanying persons, or routine clinical staff. Where the participant has provided consent for follow-up contact and has indicated a safe contact method, a trained member of the research team may review the alert according to the approved safety protocol and provide information on available referral pathways. The study team will not provide clinical diagnosis, psychotherapy, emergency monitoring, or real-time crisis intervention as part of the study. Because data are collected through a web-based, pseudonymized questionnaire and responses are not monitored continuously in real time, the study team cannot guarantee individualized emergency response to each risk-related answer. For this reason, the primary safety mechanism is the immediate automated provision of emergency, crisis, and referral information within the survey itself. If a participant independently contacts the research team and reports acute distress, suicidal intent, or risk of self-harm, a trained member of the research team will respond within one day.

The protocol will include a dedicated procedure for the ethical management of reproductive and perinatal loss or severe adverse birth-related events reported during follow-up. Additional event-specific safeguards will be applied if participants report pregnancy loss, stillbirth, neonatal loss, severe obstetric complications, or traumatic birth during follow-up. These events will be handled using a bereavement-sensitive approach. Questionnaire wording and routing will be designed to avoid assumptions about pregnancy continuation, infant survival, or parental experience, and to collect only information necessary for the study aims. Event-related responses will not trigger disclosure to partners, accompanying persons, or clinical staff through the research procedure. Where relevant, participants will be provided with neutral information on psychological, bereavement, crisis, and healthcare support options. These procedures are intended to reduce avoidable distress while allowing participants’ experiences of reproductive or perinatal loss and traumatic birth to be represented in the study if they choose to continue participation.

Several procedures will be used to mitigate potential sources of bias. Selection bias will be mitigated through systematic invitation of eligible participants during predefined recruitment periods. Because the study population will be recruited in healthcare settings and the questionnaire includes sensitive content, additional safeguards will be applied during recruitment. Study invitation will be conducted in a private or semi-private setting whenever feasible, and potential participants will not be asked about trauma exposure, suicidality-related symptoms, intimate-partner circumstances, or other sensitive domains during the initial approach. The invitation will use neutral wording focused on participation in a longitudinal study of reproductive experiences, so that the nature of a participant’s eligibility or interest in the study is not disclosed to accompanying persons. The risk of perceived coercion will be reduced by conducting recruitment through personnel who are not directly responsible for participants’ clinical care, wherever feasible. Potential participants will be able to decline immediately, request more time to consider participation, or complete the consent procedure later using the study link. Refusal to participate will not be recorded in the participant’s clinical record and will not be communicated to clinicians involved in the participant’s care, except where required for basic recruitment monitoring in anonymized or aggregate form. Participants who complete the questionnaire on site will be encouraged to do so privately, using their own device where possible. If privacy cannot be ensured, participants will be offered the option to complete the questionnaire later.

Where partners are invited as a supplementary subgroup, partner recruitment will be handled in a way that preserves the woman’s autonomy and confidentiality. Women’s participation will not require partner involvement, and partners will not be informed about women’s questionnaire responses, consent choices, or follow-up participation. Partner involvement will be treated as optional and conditional on safety, privacy, and voluntariness. Partner data will be collected through a separate consent process and separate questionnaire access, and partners will not receive access to women’s responses, consent decisions, follow-up participation, or safety-related questionnaire outputs. If there is any concern that partner recruitment, dyadic matching, or sharing of a self-generated identification code could increase pressure, surveillance, conflict, or risk to the participant, dyadic linkage will not be pursued and the woman’s individual data will remain eligible for non-dyadic analyses.

Measurement bias will be mitigated through standardized questionnaires, predefined assessment waves, programmed routing logic, and validated instruments where available. Attrition and missing-data bias will be evaluated by documenting retention across waves, examining predictors of dropout, and assessing imbalance between retained and non-retained participants. Missing data will be addressed using appropriate longitudinal estimation methods, multiple imputation for missing covariates where justified, and sensitivity analyses. Confounding will be addressed through adjusted models including theoretically selected sociodemographic, obstetric, clinical, psychological, and contextual covariates.

Additional safeguards will be applied for internally displaced participants and other participants whose safety may be affected by digital follow-up. The study will not collect GPS data, precise shelter locations, or unnecessary address information. Displacement-related information will be collected only at the level required for analysis. Follow-up communications will use neutral wording that does not disclose pregnancy, mental health, trauma, domestic violence, displacement status, or study responses. Participants will be able to choose a safe contact address, change or delete contact information, pause follow-up, or withdraw from further digital contact. Participants will also be reminded to complete the questionnaire only when privacy is available and, where relevant, to avoid using shared devices or unsafe communication channels.

Participant involvement was incorporated during protocol development to improve the relevance, acceptability, and feasibility of the study procedures. Individuals with lived experience of pregnancy planning, pregnancy, childbirth, and motherhood provided input on participant-facing materials and questionnaire content. Their feedback informed the selection and framing of study domains, the clarity of the materials, and the acceptability of study procedures.

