Following completion of the baseline survey, participants will be invited to provide contact details for the purpose of re-contact and follow-up participation. Follow-up invitations will be scheduled relative to each participant’s baseline completion date. The target assessment points will be 3, 6, and 12 months after baseline, with acceptable completion windows defined as 2.5–3.5 months for the 3-month assessment, 5–7 months for the 6-month assessment, and 10–14 months for the 12-month assessment. The exact date of questionnaire completion and the number of days since baseline will be recorded for each wave. Assessments completed outside these windows will be flagged during data management and considered in sensitivity analyses where relevant. In longitudinal models, time will be represented primarily by assessment wave, with elapsed time since baseline examined where deviations from the target schedule are substantial. Participants who agree to follow-up contact will receive invitations by email at each follow-up wave. Contact details collected for this purpose will be stored separately from questionnaire responses and will not be incorporated into the analytical dataset. Participants will retain the right to decline participation at any follow-up wave without consequence. The total duration of data collection is expected to range from approximately 3 to 12 months, depending on recruitment rates and follow-up completion.

To support study administration and data quality monitoring, the survey platform will record limited process metadata, including date of survey completion, response status, and item-level missingness. These metadata will be used solely for monitoring completeness, identifying duplicate or invalid entries where applicable, and supporting data quality review. At the end of the questionnaire, participants will be provided with information on relevant mental health and lactation support resources, together with contact details for the research team.

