Missing data and attrition will be treated as potential sources of bias, particularly because wartime mobility, distress, and changing access to healthcare may affect follow-up participation. Missingness will first be described by variable, wave, reproductive-status group, recruitment site, and partner-participation status. Intermittent missingness, where participants miss one wave but return at a later assessment, will be distinguished from permanent dropout. Reasons for missingness will be coded where available, including withdrawal, non-response, loss of contact, unsafe contact, relocation, inability to complete the questionnaire, non-consent for clinical-data extraction, and unavailable clinical records. Predictors of dropout will be evaluated using multivariable logistic regression models, and standardized mean differences will be used to quantify imbalance between retained and non-retained participants. Models will use full-information maximum likelihood estimation under a missing-at-random assumption (142). Missing covariates will be handled using multiple imputation by chained equations (RRID: SCR_026363), with estimates pooled using Rubin’s rules (143–145). Sensitivity analyses will be used to assess the robustness of primary findings. These will include complete-case analyses, inverse probability-of-censoring weighting based on estimated probability of follow-up retention, and alternative imputation specifications that include baseline distress, war-related exposure, displacement, reproductive status, and recruitment site as predictors of missingness. Where dropout appears related to psychological distress or other outcome-related variables, additional sensitivity analyses will compare primary model estimates before and after applying retention weights and after restricting analyses to participants with at least two completed waves. If results differ materially across these specifications, conclusions will emphasize the direction, size, and robustness of effects rather than a single model estimate. Baseline analyses will first be conducted for the total sample and separately by reproductive-status group. Group differences at baseline will be examined to characterize cohort heterogeneity and to identify variables requiring adjustment in longitudinal models.

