Baseline reproductive status will be included to account for cohort-entry differences between non-pregnant, pregnant, and postpartum participants. In addition, reproductive status assessed at each wave will be modeled as a time-varying covariate when participants transition between reproductive states during follow-up. Where sample size permits, interactions between time, war-related stress exposure, and reproductive status will be examined to assess whether mental-health trajectories differ across reproductive stages. Primary longitudinal analyses will be conducted in the women’s cohort. Mixed-effects growth models will include repeated observations nested within participants and will estimate mental-health trajectories across the four assessment waves. Baseline reproductive status will be included as a cohort-entry characteristic to account for initial differences between non-pregnant, pregnant, and postpartum participants.

Reproductive transitions will also be examined as secondary longitudinal outcomes. Combining groups in this framework is justified because mixed-effects models allow unequal numbers of observations, time-varying covariates, and adjustment for baseline reproductive status. Transition variables will be derived between waves, including, where applicable, becoming pregnant, giving birth, having pregnancy or neonatal loss, entering the postpartum period, remaining in the same reproductive-status group, or other documented reproductive-status changes. Binary transitions will be analyzed using generalized mixed-effects models with a logit link, whereas transitions with more than two categories will be modeled using multinomial or alternative categorical longitudinal models, depending on event frequency and model stability. These analyses will be interpreted as secondary or exploratory if the number of observed transitions is limited.

Values resulting from planned non-administration of a measure (see **Table 3**) will be coded as structurally non-applicable and will be distinguished from missing data due to item nonresponse or loss to follow-up. Structurally non-applicable values will not be imputed or treated as participant-level missingness. Analyses of cohort-specific measures will therefore be restricted to the eligible reproductive-status group or wave, while mixed-effects models will use all available repeated observations for variables applicable across groups.

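### The safety prompt can cause within-wave loss of later scales that depends on a distress score, and the planned missing-data analyses do not use that score

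*Protocol article*

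**What the plan says.** Protocol article, section 2.6.1 (Ethical considerations), sets predefined triggers, "including an SCI-2-SF score of ≥ 2, EPDS ≥ 13, GAD-7 ≥ 7, IES-R ≥ 30, or City BiTS ≥ 29". Timing is explicit: "When activated, the questionnaire will immediately display a neutral safety message". The participant then keeps full control: "They may stop the questionnaire, pause and return later, skip any item, or continue if they consider it safe and acceptable".

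Section 2.4.2 lists SCI-2-SF, EPDS, GAD-7 and City BiTS among the primary outcome measures. IES-R stands under exposure measures (2.4.1). WHO-5, on which the primary longitudinal analysis focuses (2.5), is not a named trigger.

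On missing data, section 2.5 plans full-information maximum likelihood under missing at random. The sensitivity analyses include "inverse probability-of-censoring weighting based on estimated probability of follow-up retention", alternative imputation models with baseline distress among the predictors, and a restriction to women with at least two completed waves. On coding: "Reasons for missingness will be coded where available, including withdrawal, non-response, loss of contact, unsafe contact, relocation, inability to complete the questionnaire", followed by two codes for clinical records. Planned non-administration "will be distinguished from missing data due to item nonresponse or loss to follow-up". Section 2.3 adds that "the survey platform will record limited process metadata, including date of survey completion, response status, and item-level missingness".

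**The concern.** The questionnaire itself offers a way out at the moment a distress score is high. If some women take it, the scales that come later in that sitting are missing because of that score. The trigger score is observed, so the loss could be missing at random given it, but only if an analysis uses it. The stated primary model contains time, baseline stressor burden, their interaction and reproductive status. The sensitivity analyses model who returns at follow-up. Neither names the trigger score at the wave where the questionnaire ended.

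The retained scores on later scales could then look too favourable, more so in groups that trigger more often, such as women with a high stressor burden. The cohorts also meet different numbers of triggers, which could disturb comparisons between them.

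**Working it through.** **Plan's own figure.** The article gives no trigger rate, stop rate or expected loss within a wave, so there is nothing to reproduce. The check is a reading of the text followed by an illustration with declared assumptions.

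**Step 1: triggers by cohort (Table 3).** GAD-7, IES-R and SCI-2-SF go to all women at every wave. EPDS is added for pregnant and postpartum women, and City BiTS for postpartum women.

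- Non-pregnant: 3 possible triggers
- Pregnant: 3 + 1 = 4
- Postpartum: 3 + 2 = 5

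**Step 2: does any order avoid the problem?** The scale that fires the message has already been answered; only later scales are at risk. Two triggers are primary-family scales in non-pregnant women (GAD-7, SCI-2-SF), three in pregnant women (plus EPDS) and four in postpartum women (plus City BiTS). Only one of these can come first. So at least 1, 2 and 3 primary-family scales respectively follow a trigger scale, whatever the order. WHO-5 can be fully protected by order; these scales cannot.

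**Step 3: mechanism against remedy.** The loss occurs within a sitting and depends on the current trigger score. The weights model retention between waves, the two-wave restriction counts waves, and the imputation predictor is baseline distress. At baseline that predictor could include the trigger score; at 3, 6 and 12 months it does not.

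**Step 4: illustrative size.** Assume a standard normal trigger score, a fraction p triggered, a fraction s of those stopping, and correlation r (absolute value) between the trigger score and a later scale. None of these values is in the article.

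- Mean trigger score among those triggered: m = φ(z_p)/p. For p = 0.25, m = 1.27; for p = 0.60, m = 0.64.
- Fraction lost: p × s.
- Shift of the retained mean, in SD: r × m × ps/(1 − ps).

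| p | s | r | lost | shift (SD) |
|---|---|---|---|---|
| 0.25 | 0.20 | 0.5 | 5% | 0.5 × 1.27 × 0.05/0.95 = 0.03 |
| 0.60 | 0.40 | 0.7 | 24% | 0.7 × 0.64 × 0.24/0.76 = 0.14 |

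With lower stop rates (p 0.20 to 0.80, s 0.05 to 0.30, r 0.5 to 0.7) the same formula gives a smaller range. At p = 0.20, m = 1.40, and the shift is 0.5 × 1.40 × 0.01/0.99 = 0.007. At p = 0.50, m = 0.80, and it is 0.7 × 0.80 × 0.15/0.85 = 0.10.

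**Step 5: difference between burden groups.** Suppose 25% of low-burden and 60% of high-burden women trigger, and 40% stop in both groups. Then 10% and 24% of later scores are lost.

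- r = 0.5: low 0.5 × 1.27 × 0.10/0.90 = 0.07; high 0.5 × 0.64 × 0.24/0.76 = 0.10; difference 0.03 SD.
- r = 0.7: low 0.10; high 0.14; difference 0.04 SD.

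This is a distortion at one wave. If trigger and stop rates are stable across waves, it largely cancels from the baseline-to-12-month contrast. It stays in that contrast to the extent that the rates change differently in the two groups.

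**The case against.** **The principal outcome may be untouched.** This stands. WHO-5 is not a trigger, and Tables 1 and 3 list it before all five trigger scales. Those tables do not give a presentation order, but nothing in the article points the other way. If WHO-5 comes first, its within-wave loss from this cause is zero. A reader might infer that the primary analysis is biased; the article does not support that.

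**Loss is possible, not certain.** This stands too. Women may continue, or pause and return, and they could already skip items or withdraw without the prompt. How much extra break-off the message causes is unknown. Nor can the loss be placed in the most distressed women in particular: IES-R is scored 22 to 110 in Table 1, so its trigger of 30 lies 8 of 88 points above the minimum and may reach women with few symptoms.

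**Coding is not clearly deficient.** This largely stands. The list of reasons is open and contains near matches, and item-level missingness is recorded. The review of alerts in section 2.6.1 implies that activation is known for at least some women. The data-management plan, which is not shown, may hold more codes. If partial responses are kept, a score at threshold followed by missing items would identify a break-off after the message, though not the choice made. The lack of a named code would not be a finding by itself.

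**The models recover part of the loss.** Partly. Full-information maximum likelihood uses a woman's scores at other waves, which the complete-case formula ignores, so the shifts above may be too large. The extra analyses for distress-related dropout still work through retention weights and completed waves. They do not use the score that opened the prompt.

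**Conclusion.** The point holds as a mismatch between a stated mechanism and a stated remedy. The prompt can make the loss of later scales depend on a same-wave distress score, and that loss is not missing at random given the variables named in the models. The number of possible triggers also differs by cohort: three, four and five.

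WHO-5 is exposed only if it is placed after a trigger scale, which the article does not say. For the other primary-family outcomes some exposure is unavoidable, and its size is unknown. Under the assumed ranges (25 to 60% triggered, 20 to 40% of those stopping, correlation 0.5 to 0.7), 5 to 24% of later scores are lost at a wave, the complete-case mean shifts by about 0.03 to 0.14 SD, and the difference between burden groups shifts by about 0.03 to 0.04 SD.

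It is tempting to conclude that burden-by-time effects will be shrunk. In the worked example the difference at a single wave is attenuated, but the effect on change depends on how trigger and stop rates move over time, and the documents give no basis for that. This is a near-costless improvement, not a flaw that threatens the primary result.

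**What to change.** Leave the thresholds, the message and the participant's options as they are.

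1. State the order of scales, with WHO-5 before every trigger scale at each wave, and save responses page by page.
2. Log at each wave whether the pathway was activated, by which scale, and what the woman chose (stop, pause or continue). A stop after the message can then be separated from other non-completion.
3. For outcomes placed after a trigger, add activation and the same-wave trigger score as auxiliary predictors in the weighting and imputation sensitivity analyses.

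The cost is some survey programming before launch, which can be tested in the pilot of survey routing already planned in section 2.4, plus a few logged fields and extra predictors in models that are already planned. Participants carry no added burden.
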